#### Cost-Effectiveness Analyses

Quality-adjusted life years (QALYs) will be used for economic evaluation to compare the relative costs and outcomes of different groups. Estimating quality of life weights involves quantifying the quality of life at different health states on a scale from 0, representing the worst imaginable health state or death, to 1, indicating perfect health. These weights are directly measured in this study population using standardized instruments (ie, EQ-5D-5L). To calculate QALYs, the quality of life weights are multiplied by the duration spent in each health state, with the results summed over the study period. Direct health care utilization, such as outpatient visits and prescribed medications, will be recorded, while indirect costs are excluded because most expected participants are secondary- or early tertiary-level students without a full-time income. Incremental cost-effectiveness ratios will then be calculated as the difference in mean cost divided by the difference in mean QALYs between the OkeyMind and waiting list groups.

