**Methods:**

Participants aged 15 years through 24 years with mild or more severe social phobia (Social Phobia Inventory [SPIN] ≥25) and access to WeChat will be recruited and screened onsite and then randomly assigned to the intervention or waiting list control group. The study will recruit 180 participants, with 90 in each group. The intervention group will receive a 1-month mobile psychoeducation program (OkeyMind), which includes both psychoeducation and meditation components, with all content fully automated. The waiting list control group will receive the same intervention after 3 months. The primary outcome is social anxiety symptoms measured using SPIN. Secondary outcomes include depression (Patient Health Questionnaire-9) and health-related quality of life (EuroQol-5). Assessments will be conducted at baseline, postintervention, and a 3-month follow-up.

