### Research Objectives and Hypotheses

The primary objective is to assess the effectiveness of the OkeyMind mobile-based psychoeducation program on mitigating social anxiety symptoms among young adults aged 15 years through 24 years. The secondary objective is to evaluate the cost-effectiveness of the OkeyMind program as a mental health intervention tool, aiming to ascertain whether the financial investment in OkeyMind translates into significant economic and health-related advantages. The study tests 2 hypotheses: (1) OkeyMind is more effective than the control condition in reducing social anxiety symptoms among youths, and (2) OkeyMind is more cost-effective than the control condition for this population.

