### Outcomes

Basic demographic and clinical data, including age, gender, region, and socioeconomic status, will be collected. The primary outcome will be social anxiety symptoms, assessed using SPIN. Secondary outcomes include depressive symptoms, measured using the Patient Health Questionnaire-9 (PHQ-9), and quality of life, evaluated using the EQ-5D-5L, which will also be used for cost analysis. All outcomes will be self-assessed using online measurements at baseline, postintervention, and the 3-month follow-up (Figure 2).

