### Analysis

#### Effectiveness Analyses

The primary hypothesis for the between-group difference in the primary outcome will be tested using a linear mixed-effects model. This model accounts for responses at postintervention and the 3-month follow-up, incorporating baseline outcome measures and intervention assignment as fixed effects, with a participant-specific random intercept. An interaction between time and the randomized group will also be fitted as a fixed effect to allow estimation of treatment effect at all time points. A similar approach will be used for the secondary outcome analysis. The imputation of missing values will be based on the assumption that data are missing at random. The primary analyses will follow the intention-to-treat principle, meaning participants will be analyzed based on their originally assigned groups, regardless of their adherence to entry criteria, the treatment received, or any withdrawal or deviation from the protocol [39]. The data will be automatically generated by the WeChat miniprogram once participants complete the process, eliminating the need for manual data entry. A *P* value <.05 will be used as the level of statistical significance. Data analysis will involve at least 2 statisticians or researchers and will be processed and verified using various statistical software, such as SAS and SPSS.

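### The cost-effectiveness section states no adjustment of the QALY difference for baseline EQ-5D-5L, which costs precision in a very small ICER denominator

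*Protocol article*

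**What the plan says.** Under Cost-Effectiveness Analyses, the article takes its utilities from the trial participants: "These weights are directly measured in this study population using standardized instruments (ie, EQ-5D-5L". QALYs are then formed so that "the quality of life weights are multiplied by the duration spent in each health state, with the results summed over the study period". The ICER is "calculated as the difference in mean cost divided by the difference in mean QALYs between the OkeyMind and waiting list groups". That section mentions no covariate.

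Under Outcomes, EQ-5D-5L has two roles: "quality of life, evaluated using the EQ-5D-5L, which will also be used for cost analysis". It is measured three times: "All outcomes will be self-assessed using online measurements at baseline, postintervention, and the 3-month follow-up".

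Under Effectiveness Analyses, the primary model is described as "incorporating baseline outcome measures and intervention assignment as fixed effects", and the secondary outcomes are to be handled in a similar way. EQ-5D-5L as an outcome is therefore baseline-adjusted. The article does not say whether the same holds once EQ-5D-5L has been turned into QALYs.

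Under Research Objectives and Hypotheses, cost-effectiveness is the second of two hypotheses: "OkeyMind is more cost-effective than the control condition for this population".

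**The concern.** A participant's QALY starts from the utility at baseline. Baseline utility enters the QALY directly, as part of the area under the curve, and indirectly, because people who start higher tend to stay higher. Neither part can be due to the intervention. Any chance difference between the arms at baseline therefore shows up partly as a QALY difference.

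Over 3 or 4 months, the QALY difference that a realistic utility gain can produce is only a few thousandths to about 0.015. A chance shift of similar size changes the ICER a great deal, and if the QALY difference changes sign, the ratio reads the opposite way.

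The baseline-adjusted mixed model for the outcomes does not fill the gap as written. A QALY is one total per participant, with no repeated visits and no baseline value of its own. The covariate has to be named separately, as baseline EQ-5D-5L.

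**Working it through.** The article states no utility, QALY or ICER figure, so there is nothing of its own to reproduce.

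**Inputs from the article**
- Utility at T0, T1 and T2. T1 is at 1 month (Abstract: "The intervention group will receive a 1-month mobile psychoeducation program (OkeyMind"). T2 is at 3 months if the follow-up is counted from baseline, or 4 months if counted from T1. The text does not settle this, so both are shown.
- 90 per arm with 10% attrition: 90 × 0.9 = 81 per arm.

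**Assumed, not in the article**
- Utility SD *s* = 0.10-0.20, equal at each visit.
- Correlation *r* = 0.4-0.8 between any two visits.
- True utility gain *g* = 0.02-0.05 at T1 and T2.
- Trapezoidal area under the curve.

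**Step 1. Weights on T0, T1, T2 (years)**
- 3 months: 1/24, 1/8, 1/12 (0.0417, 0.1250, 0.0833). Total *H* = 0.25; T0 share 1/6.
- 4 months: 1/24, 1/6, 1/8 (0.0417, 0.1667, 0.1250). Total *H* = 0.333; T0 share 1/8.

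**Step 2. True QALY gain** = *g*(w1 + w2)
- 3 months: 0.2083*g* = 0.0042 to 0.0104.
- 4 months: 0.2917*g* = 0.0058 to 0.0146.

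**Step 3. Carry-through of a baseline imbalance.** The regression slope of QALY on baseline utility is b = w0 + *r*(w1 + w2). The fraction carried through, relative to the horizon, is b/*H*.

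**Step 4. Variance.** In units of *s*² × 2/81, the unadjusted variance of the QALY difference is v = (1 − *r*)Σw² + *rH*². After adjustment for baseline utility it is v − b².

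| *r* | b/*H*, 3 mo | variance cut, 3 mo | b/*H*, 4 mo | variance cut, 4 mo |
|---|---|---|---|---|
| 0.4 | 50% | 39% | 48% | 35% |
| 0.5 | 58% | 49% | 56% | 45% |
| 0.6 | 67% | 59% | 65% | 55% |
| 0.7 | 75% | 69% | 74% | 66% |
| 0.8 | 83% | 79% | 83% | 77% |

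**Step 5. Shift from a 1-SE baseline imbalance** = b × *s*√(2/81). The imbalance itself is 0.0157 for *s* = 0.10 and 0.0314 for *s* = 0.20.
- Smallest (*s* 0.10, *r* 0.4, *g* 0.05, 4 months): 0.1583 × 0.0157 = 0.0025, against a gain of 0.0146, or 17%. With *r* = 0.5 it is 20%.
- Largest (*s* 0.20, *r* 0.8, *g* 0.02, 3 months): 0.2083 × 0.0314 = 0.0065, against a gain of 0.0042, or 157%.

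**Step 6. Worked case** (*s* 0.15, *r* 0.7, *g* 0.03, 3 months)
- 1-SE imbalance: 0.15 × √(2/81) = 0.0236.
- b = 0.0417 + 0.7 × 0.2083 = 0.1875, so the shift is 0.0044 against a gain of 0.00625 (71%).
- v = 0.3 × 0.0243 + 0.7 × 0.0625 = 0.0510; adjusted 0.0510 − 0.1875² = 0.0159.
- SE unadjusted: 0.0236 × √0.0510 = 0.0053. SE adjusted: 0.0236 × √0.0159 = 0.0030.
- Chance that the estimated QALY difference has the wrong sign, Φ(−gain/SE): 12.0% unadjusted, 1.8% adjusted. Over 4 months: 11.0% and 1.7%.

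**The case against.** The strongest reply is that silence is being read as a choice. The sentence on the ICER is the textbook definition. It fits a model-adjusted mean difference as well as a difference of raw arm means, and the words raw and unadjusted do not appear. A condensed article commonly leaves covariates to an analysis plan, and none is shown here. This stands as far as it goes: a reader might infer that the trial has decided on raw means, and the article does not support that. Nor do the two analysis sections contradict each other, since the rule for secondary outcomes is neither extended to QALYs nor withheld from them. What remains is that the article fixes an estimator for a stated objective, and that estimator, followed literally, omits baseline utility.

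Three further readings go too far:
- **Bias.** A reader might infer a biased ICER. Under randomisation the QALY difference is not biased on average; the cost is extra variance and an imbalance in the particular sample drawn.
- **Full pass-through.** Only about half to four fifths of an imbalance carries through, and T0's own share of the area is 1/6 or 1/8.
- **No test of the second hypothesis.** A reader might infer that the trial has no means of testing it because only a ratio is given. A net-benefit threshold, bootstrap and acceptability curve are ordinary SAP content, so their absence from an article is not a defect.

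The size also depends on an assumed SD, correlation and gain, and on trapezoidal weighting. Varying them changes the size widely. Within these ranges, adjustment always improves precision.

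**Conclusion.** The point holds as a matter of precision and clarity. The cost-effectiveness section states no baseline-utility adjustment for QALYs, while the effectiveness section adjusts EQ-5D-5L as an outcome. Across the assumed ranges in the working, a 1-SE imbalance shifts the QALY difference by 17% to 157% of the true gain, and adjustment cuts the variance by 35-79%. These are conditional illustrations, because the article supplies none of the utility inputs. The objective affected is secondary, and the primary SPIN analysis is untouched. Adjustment sharpens the denominator but does not make it large, so the ICER will still need care in reading.

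**What to change.** Add one sentence to the cost-effectiveness section (and to the SAP, if it does not already say so): the incremental QALY is estimated by regressing each participant's QALY on randomised arm and baseline EQ-5D-5L index, and the ICER uses this adjusted difference as its denominator.

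The cost is a sentence and one regression. Baseline EQ-5D-5L is already collected from every participant, so no new data are needed, and the article's timeline places analysis after data collection ends. Adjusting the numerator for baseline cost is not part of this request, because the article does not say that pre-baseline costs are collected.

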## Results

The study was funded in April 2024, and the first participant was enrolled in September 2024; as of the end of March 2025, 132 participants had been recruited. Recruitment is ongoing. Data collection will conclude in July 2025, after which data analysis will begin and be completed in August 2025, with primary findings targeted for publication in spring 2026. The study’s design, management, analysis, and reporting are independent of the funder.

Demographic features, such as age, gender, and education level, will be reported to provide a comprehensive overview of the participant population. The primary analysis, focusing on social anxiety, will be conducted using an intention-to-treat approach, carefully accounting for missing values. Various visualizations, including trend graphs, charts, flow diagrams, and other illustrative tools, will be used to depict participants’ changes over time. Additionally, subgroup analyses will be included to explore variations within specific segments of the participant population.

Metrics such as intensity and frequency of use will also be reported to offer insights into participants’ engagement with the intervention. Last, any significant changes in the software or delivery of the intervention during the study period will be documented and reported to ensure transparency and to contextualize the findings.

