### Recruitment

The study will be conducted in school settings, including middle schools and tertiary institutions, across China. The trial aims to enroll 180 participants, with 90 assigned to each group [28]. This sample size accounts for an anticipated attrition rate of 10% and is expected to offer 90% statistical power. This determination is based on using an independent group *t* test, a significance level of .05, and an effect size of 0.35 (Cohen *d*), which falls within the small-to-medium range [29]. To recruit enough participants, school faculty help with recruitment, and digital flyers and promotional videos are shared through WeChat and school online platforms.

The participant inclusion criteria include (1) youths aged between 15 years and 24 years old who are (2) exhibiting mild or more severe social phobia (ie, Social Phobia Inventory [SPIN] score ≥25) and (3) have a smartphone with WeChat installed and basic internet literacy. The exclusion criteria include (1) being unable to attempt a baseline assessment (eg, due to being unpermitted to leave a psychiatric ward), (2) currently receiving another intensive psychological intervention, (3) currently holding an active suicidal plan, and (4) having a current diagnosis of psychological disorders (eg, schizophrenia, bipolar disorder). These data will be collected through self-report questionnaires, including questions such as: “Have you been previously diagnosed with any psychological disorders (eg, schizophrenia, bipolar disorder)? If yes, please specify.” Additionally, university tutors, who are familiar with students’ mental health conditions, will assist with identifying ineligible participants. Participants will be recruited and screened offline but will complete all interventions and assessments online. Participants are briefed through online tutorial video clips in the OkeyMind miniprogram; these clips demonstrate the research flow regarding intervention timing, follow-up frequency, and usage intensity.

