OkeyMind features 3 main modules: self-learning module, psychological assessment tools, and meditation demonstrations. Participants can simply search “OkeyMind” on the WeChat miniprogram platform and access it free of charge. The mobile psychoeducation program (OkeyMind), based on the WeChat miniprogram, includes both psychoeducation and meditation components. Participants will complete the components as well as the psychological assessment tools at their own pace. For meditation practices, a tutorial video will be provided for guidance. All content is fully automated. No co-intervention will be provided alongside OkeyMind. To prevent delays in the intervention or follow-up assessments, an automated reminder function was developed. This feature ensures that participants receive pop-up reminders via WeChat if any delays occur. Trained research assistants will remind participants to engage in the activities (eg, intervention sessions, assessments) according to the study timeline and will be available to answer questions via social media platforms (eg, WeChat), phone calls, or messages.

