#### Control Group—Waiting List

Participants in the waiting list control group will have access to the OkeyMind intervention withheld until after the 3-month follow-up assessment. To prevent confounding effects from relevant concomitant care and interventions, participants will be required to refrain from receiving any other treatments or interventions specifically targeting social phobia during the study period.

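### A July 2025 end of data collection does not fit 180 participants with a 3-month follow-up when only 132 had been recruited by the end of March and recruitment was still open

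*Protocol article*

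**What the plan says.** The Recruitment section sets the target: "The trial aims to enroll 180 participants, with 90 assigned to each group". It allows for 10% attrition. On progress, the Results section says that "the first participant was enrolled in September 2024" and that "as of the end of March 2025, 132 participants had been recruited. Recruitment is ongoing". It gives no closing date for recruitment and no reduced target. It then gives the end of the study: "Data collection will conclude in July 2025, after which data analysis will begin and be completed in August 2025". The Results paragraph of the abstract repeats these dates.

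Assessments are at baseline (T0), after the intervention (T1) and at a 3-month follow-up (T2), according to Trial Design and Outcomes. The programme lasts 1 month (abstract, Methods). Effectiveness Analyses puts both T1 and T2 into the primary mixed model. Cost-Effectiveness Analyses sums QALYs over the study period from the EQ-5D-5L, so T2 is their last measurement.

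The text shown does not say whether the 3 months run from baseline or from the end of the programme. Two statements on the waiting list bear on this. The abstract says: "The waiting list control group will receive the same intervention after 3 months". The Control Group—Waiting List section says that access is "withheld until after the 3-month follow-up assessment".

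**The concern.** Each participant needs at least three months between enrolment and T2. With 48 still to be recruited at the end of March, a close four months later leaves little or no room for them. If the date were followed as written, one of two things would happen. Either the trial would stop short of 180 without saying so, or late enrolees would have no T2. T2 feeds both the primary model and the QALYs, and a follow-up not collected on time cannot be recovered later.

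The unstated origin of the 3 months matters because it moves the last possible enrolment date by a month and sets the length of the QALY period.

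**Working it through.** **Inputs.** Target 180 (Recruitment). First enrolment in September 2024, day not given, so taken as 1 to 30 September (Results). 132 recruited by 31 March 2025 (Results). Programme of 1 month (abstract, Methods). Close in July 2025, taken as 31 July, the most favourable day (Results). A month is counted as 30.44 days, and enrolment and baseline are treated as the same day. T2 is taken at month 3 or month 4 from baseline.

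**1. When the stated July date works.** Remaining participants: 180 − 132 = 48. The latest enrolment that still gives T2 by 31 July is:
- T2 at month 3: 31 July minus 3 months, about 30 April to 1 May.
- T2 at month 4: 31 July minus 4 months, about 31 March to 1 April.

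So July is reproduced for 180 participants only with T2 at month 3 and all 48 enrolled in April. With T2 at month 4, July fits a trial that closed recruitment at 132 on 31 March, but the article says that recruitment was continuing.

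**2. Pace so far.** From 1 September to 31 March is 211 days, or 6.93 months; from 30 September it is 182 days, or 5.98 months.
- 132 / 6.93 ≈ 19.0 per month
- 132 / 5.98 ≈ 22.1 per month

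Enrolling 48 in one month would be 48 / 22.1 ≈ 2.2 to 48 / 19.0 ≈ 2.5 times that pace.

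**3. Projected end at that pace.** The 48 take 48 / 22.1 ≈ 2.2 to 48 / 19.0 ≈ 2.5 months, so enrolment ends about 5 to 15 June 2025.
- Last T2 at month 3: about 4 to 14 September.
- Last T2 at month 4: about 4 to 14 October.

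Both fall after the July close and after the August end of analysis.

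**4. T2 missing at a 31 July close.**

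| T2 at | Of the 48, enrolled in time | Without T2 | Share of 180 |
|---|---|---|---|
| Month 3 | 19.4 to 22.5 | 28.6 to 25.5 | 15.9% to 14.2% |
| Month 4 | under 1 | about 47 | about 26% |

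An earlier day in July makes this worse: with a 1 July close and T2 at month 3, about 47 of the 48 (26% of 180) would already miss T2.

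**5. Against the allowance.** The plan allows for 10%, or 18 of 180, leaving 162. If 10% dropout were added independently to the administrative loss, T2 would be available for about 0.9 × 151.4 = 136 to 0.9 × 154.5 = 139 participants (month 3), or 0.9 × 132.6 = 119 (month 4).

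**6. T1.** The last enrolment in early to mid-June plus 1 month is early to mid-July. At a 31 July close, T1 is therefore still reached by all.

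**The case against.** The strongest reply is that July 2025 is a forecast in a status report, not a rule. Nothing in the article says that follow-up stops on a calendar date or that participants without T2 by then are dropped. The operative text is the target of 180 and assessment of everyone at three times. This stands: a reader might infer that T2 will be cut off, but the documents show only that the date and the design disagree. The date may simply slip.

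The size of the loss is also a projection. Recruitment runs through schools, no monthly figures are given, and accrual need not be constant. A burst of 48 in April with T2 at month 3 would just fit, although none is announced.

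Four stronger readings are tempting, and the text does not support them:
- *Controls are treated before T2.* This arises only if T2 is at month 4. With T2 at month 3 from baseline, the abstract and the Control Group—Waiting List section agree, and together they lean that way.
- *T1 has no defined time in the control arm.* Outcomes points to Figure 2 for the schedule. That figure is not shown, and visit days are often left to the full protocol.
- *Outcome assessments are self-paced.* The sentence "Participants will complete the components as well as the psychological assessment tools at their own pace" sits in the description of the app, where the assessment tools are one of its three modules. The same section describes reminders and prompting to the study timeline.
- *The calendar is what leaves the trial underpowered.* For d = 0.35 and a two-sided t test at .05, the full 90 per arm gives only about 65% power. That shortfall is a separate matter.

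Missingness set by enrolment date would fall on both arms, and the mixed model would still use T1.

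**Conclusion.** The point holds as a conflict between the timeline and the design. A target of 180, open recruitment at 132 by the end of March, and a July close are compatible only under month-3 timing with all 48 enrolled in April. They are incompatible under month-4 timing. The calendar limits rest on the article's own dates.

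The projected loss of 14–16% (month 3) or about 26% (month 4) rests on three assumptions: average accrual continues, the close is on 31 July, and the close is applied literally. On either reading it exceeds the 10% allowed for all attrition. What would be lost is T2 precision for SPIN and the last EQ-5D-5L point for the QALYs. The documents give no ground for claiming bias between arms or that the sponsor intends to truncate follow-up. The unstated origin of the 3 months is the lesser part, since Figure 2 may settle it.

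**What to change.** In the Results section and the Results paragraph of the abstract, replace the July 2025 date with a rule: data collection ends when the last randomised participant has completed T2 or passed the T2 window, and analysis starts after that. A projected date can stand beside the rule. If the sponsor instead means to stop below 180, the article should say so.

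In the same edit, state the day from which the 3 months run, the same in both arms, so that the abstract and the Control Group—Waiting List section are reconciled.

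The cost is a timeline amendment. At the average pace the last T2 comes 35 to 45 days after 31 July (month 3) or 65 to 75 days after it (month 4). Allowing for a visit window, a delay of about 2 to 3 months should be enough. Analysis in late 2025 still allows publication in spring 2026. The change should be made before the July close is applied.
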